## 7. TRIAL DESIGN

SCALE is a cluster-randomised trial of TB/HIV active case-finding with constrained randomization (1:1 ratio) of 72 clusters of ~4,400 adults per cluster, with boundaries defined by community health worker catchment areas

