### 13. ECONOMIC EVALUATION

The main objective of the economic evaluation is to estimate the affordability and cost-effectiveness of the TB/HIV ACF intervention with the main focus being the TB intervention.

Specifically, we will estimate the incremental cost-effectiveness of ACF in comparison to facility-based case-finding only. To achieve this, inputs (costs) and outputs will be estimated.

Effectiveness data will be provided by:

1. Numbers of additional patients started on TB treatment, both a) following detection of undiagnosed patients by the ACF and b) as evidenced by differences between trial arms in notification rates identified through the Blantyre District Electronic TB Register (“additionality”)
2. Numbers of **new TB cases** and **TB deaths** averted as estimated from fitting an established HIV and TB model (13) to pre-intervention and post-intervention survey data and case-notifications.

Key outputs will be:

1. Incremental costs per additional individual started on TB treatment (using both direct diagnosis by the ACF team and additionality capture by the Electronic TB Register)
2. Incremental costs per DALY, new TB case, new TB infection and TB death averted

Two economic evaluations will be undertaken: firstly, a within trial evaluation; and secondly, projection a fully-costed dynamic transmission model. Both will be used to estimate the expected incremental cost per disability-adjusted life year (DALY). The mathematical model will estimate TB infection, case and TB death averted. For each analyses, the perspective will be that of the provider, and will only include the direct intervention and medical costs.

The within trial evaluation will adopt a time horizon matching the length of intervention in the trial, with no need to discount costs or DALYs given that the intervention is brief. The model-based evaluation will adopt a 20 year horizon, with future costs and DALYs discounted at 3.5%, and sensitivity analysis to explore alternative discount rates.

The primary analysis will focus on the direct intervention and the broader healthcare costs. This will include the costs of TB and HIV screening, the costs incurred in linking participants to TB/HIV services and any associated staff costs.

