The healthcare resources used will be captured prospectively and primary costing studies will be undertaken to estimate the unit costs for these identified resources. The broader healthcare resource use will be captured through interview of patients who are SCALE cluster residents (both intervention and non-intervention arms) starting TB treatment at routine facilities.

The provider-costs of treating TB will be estimated from previously collected inpatient data (43,44) and from interview of TB outpatients and District Health staff to establish:

- Outpatient clinic visits
- Days of inpatient hospital care
- Medications
- Investigations and procedures

As Malawi Ministry of Health does not have reference costs for these healthcare resources, previous unit costs estimated in Malawi will be used to derive total costs.

Mean costs and outcomes for the ACF model used in SCALE will be estimated, together with the mean incremental cost-effectiveness ratio. Measures of uncertainty (standard errors and confidence intervals) will also be reported for the mean estimates.

Sensitivity and scenario analysis will also be considered. This will include undertaking a cost-effectiveness analysis where the primary outcome will reflect two outcomes being evaluated in the trial: the proportion of participants with undiagnosed or untreated TB. As missing data is a common occurrence in trials, additional analysis will explore impact of missing data and alternative approaches to account for missing data.

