## 14. STATISTICS

### 14.1. Sample size justification

Sample sizes were initially calculated assuming a decline from the last National TB Prevalence Survey in 2013-14 given that there has been case-finding activity since then. However, the interim results from a **pre-intervention survey** show greater than anticipated decline (target of 14,511 participants will give precision of +/- 2.5 around an assumed true prevalence of 900 per 100,000 adults, assuming design effect of 1.5 from random household sampling. The increase to 15,500 allows for wastage from e.g. unreadable Xray/contaminated cultures).

Sample size calculations and statistical analyses will use established approaches for cluster-randomised trials.

The **primary trial outcome** has been changed from self-reported testing outcome to TB case notification.

For this, we assume an annual case-notification of adult microbiologically-confirmed TB to be in the range of 70 to 100 per 100,000 adults for the standard of care clusters, based on current data and trends.

An adult population of ~150,000 per arm followed over 12 months will then provide power to detect a 44% to 56% increase in microbiologically confirmed TB if  $k = 0.3$  to  $0.4$ .

Analysis will use standard methods appropriate for cluster-randomised trials, with adjustment for pre-intervention rates of adult microbiologically-confirmed TB.

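### A standard error for the incremental cost-effectiveness ratio is unstable wherever its denominator is a between-arm difference that can reach zero; report uncertainty on cost and effect instead

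*Combined protocol and SAP*

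**What the plan says.** Section 13 (Economic evaluation) will estimate mean costs and outcomes for the ACF model, "together with the mean incremental cost-effectiveness ratio. Measures of uncertainty (standard errors and confidence intervals) will also be reported for the mean estimates". The mean estimates in that sentence naturally include the ratio.

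The denominators come from the same section. One measure of effectiveness is the number of additional patients started on treatment, "as evidenced by differences between trial arms in notification rates identified through the Blantyre District Electronic TB Register". The first key output, incremental cost per additional person started on treatment, is to be calculated "using both direct diagnosis by the ACF team and additionality capture by the Electronic TB Register", so it has two versions. The second key output is "Incremental costs per DALY, new TB case, new TB infection and TB death averted". The within-trial evaluation and the transmission model both contribute to the cost per DALY; cases, infections and deaths averted come from the model.

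The only other work on uncertainty is "Sensitivity and scenario analysis will also be considered", together with missing-data analyses and alternative discount rates. No Fieller interval, bootstrap, net benefit, cost-effectiveness plane or acceptability curve is named. Section 14.2 leaves detail to an analysis plan still to be written.

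**The concern.** A between-arm difference in notifications can be estimated as zero or negative even when the intervention works. A ratio with such a denominator has no finite variance, so its standard error has no value to settle on. The ratio also jumps from very large positive to very large negative values as the effect crosses zero, and a negative value can mean either dominance or its opposite. An interval of the form estimate plus or minus 1.96 standard errors cannot represent this.

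Cost per additional person treated is a figure that a programme would use when deciding on scale-up. At stake is an upper limit that is too low and, in many plausible trials, a lower limit that is a negative cost. The primary outcome analysis is not affected.

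**Working it through.** **Inputs.** 36 clusters per arm, from "constrained randomization (1:1 ratio) of 72 clusters of ~4,400 adults per cluster" (section 7). From section 14.1: a control rate "in the range of 70 to 100 per 100,000 adults for the standard of care clusters" per year, k = 0.3 to 0.4, and the statement "An adult population of ~150,000 per arm followed over 12 months will then provide power to detect a 44% to 56% increase". The primary-outcome window is 3 months in section 9.1, while the table there and section 14.1 use 12 months, so both are shown.

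**1. Reproducing the plan's figure.** For an unmatched cluster trial comparing rates,

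c = 1 + (z_α/2 + z_β)² × [(λ0 + λ1)/y + k²(λ0² + λ1²)] / (λ1 − λ0)²,

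with c = 36 and y = 150,000/36 = 4,167 person-years per cluster. Section 14.1 states neither power nor significance level. Assuming 80% and two-sided 5%, the detectable increase is 44.0% (rate 100, k 0.3) to 56.7% (rate 70, k 0.4), which matches 44% to 56%. At 90% power it would be 52.1% to 67.7%. The variance formula is therefore a fair basis for what follows.

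**2. Precision of the register-based effect.** SE = √{[(λ0 + λ1)/y + k²(λ0² + λ1²)]/36}. Take 3 months (y = 1,042) and a true 50% increase:

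- Rate 100, k 0.3: (2.400 + 0.2925) × 10⁻⁶ / 36 gives SE 2.735 × 10⁻⁴. The difference is 5.0 × 10⁻⁴, so z = 1.83 (about 19 extra cases, SE 10).
- Rate 70, k 0.4: (1.680 + 0.2548) × 10⁻⁶ / 36 gives SE 2.318 × 10⁻⁴. The difference is 3.5 × 10⁻⁴, so z = 1.51 (about 13 extra cases, SE 9).

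The chance that the 95% interval for the effect includes zero is Φ(1.96 − z) − Φ(−1.96 − z), which is 55% and 67%. In those trials Fieller's set for the ratio is unbounded. The chance that the estimate is negative is Φ(−z), 3% and 7%.

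**3. Other windows and effects** (ranges over rate 70-100 and k 0.3-0.4).

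| Window | True increase | z | Effect interval includes zero |
|---|---|---|---|
| 3 months | 20% | 0.65-0.79 | 88-90% |
| 3 months | 44-56% | 1.35-2.02 | 48-73% |
| 3 months | 50% | 1.51-1.83 | 55-67% |
| 3 months | 100% | 2.71-3.29 | 9-23% |
| 10 months | 50% | 2.41-2.98 | 15-33% |
| 12 months | 20% | 1.12-1.39 | 72-80% |
| 12 months | 44-56% | 2.29-3.50 | 6-37% |
| 12 months | 50% | 2.56-3.18 | 11-28% |
| 12 months | 100% | 4.44-5.55 | under 1% |

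**4. Coverage of a symmetric interval, if one were used.** Treat cost as fixed, so the ratio is proportional to 1/e with delta-method SE s/e². Write u for the estimate divided by the true effect, and c = 1.96/z. The interval covers when |u − u²| ≤ c. For c ≥ 1/4, which holds in every row above, this means u lies between (1 − √(1 + 4c))/2 and (1 + √(1 + 4c))/2. At a 50% increase:

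- 3 months, z = 1.51: u from −0.744 to 1.744, coverage 86.5%. With z = 1.83 it is 88.1%.
- 12 months, z = 2.56 and 3.18: 90.3% and 91.5%.

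Every miss leaves the whole interval below the true ratio. The lower limit is negative whenever e < 1.96s, so in essentially the same 55-67% of trials at 3 months.

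**5. The standard error itself.** With assumed figures (incremental cost 100,000, SE 10,000; 33 extra cases, SE 13.4), the ratio at the means is 3,030. The standard deviation of simulated ratios was about 38,000 with 10⁴ draws, 78,000 with 10⁵ and 674,000 with 10⁶. More computing does not produce an answer.

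**The case against.** The strongest reply is that section 13 does not say the interval is symmetric. Fieller and bootstrap intervals are confidence intervals too, and both fit the sentence. That stands: the coverage figures describe one possible method, not one the plan states. It does not rescue the standard error, which the sentence promises and no interval method repairs.

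Other parts of the reply also stand:

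- The direct-diagnosis version of the first key output has a count as its denominator and cannot go negative. The 20-year model ratios are outside these calculations.
- The rate of 70-100 is for microbiologically confirmed TB, whereas section 13 counts patients started on treatment without that restriction. The true z for the economic denominator is unknown in either direction.
- Adjustment for pre-intervention rates (section 14.1), randomisation balanced on notification rates (section 8.1) and the Synopsis figure of about 160,000 adults per arm would tend to raise precision. Ignoring uncertainty in cost works the other way.
- The within-trial horizon is the length of the intervention, which the document gives as 10-11 months or a year, beside 1-3 months of follow-up per cluster.

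A reader might infer that the effect will often be near zero here. The documents do not support that as a general statement. It holds over 3 months at the increases the trial was powered for, but not over 10-12 months under the doubling of smear-positive notifications that section 5.1.2 reports from Blantyre. The low interim prevalence in section 5.1.1 makes a smaller effect more plausible without establishing it. A reader might also infer that the economic analysis ignores clustering; section 14.1 promises cluster-trial methods for the statistical analyses in general, and section 13 merely does not repeat this.

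**Conclusion.** The point holds for the within-trial ratios with a between-arm denominator: register-based cost per additional patient treated, and within-trial cost per DALY. For these the promised standard error is a poor statistic, and the interval method is unstated.

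The practical size depends on the window and the true effect. At a 50% increase the effect interval includes zero in 55-67% of trials over 3 months and 11-28% over 12 months; a symmetric interval would cover about 87-88% and 90-92% respectively, always missing on the cheap side. With a doubling the chance of including zero falls to 9-23% and under 1%. These figures rest on confirmed TB, 36 clusters and 150,000 adults per arm, normal approximations, no baseline adjustment and no cost uncertainty. No figure was derived for DALYs. The point concerns a secondary analysis and is worth correcting because the plan should work across this whole range.

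**What to change.** In section 13, or in the analysis plan promised by section 14.2, replace the sentence on uncertainty with wording such as:

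*The incremental cost-effectiveness ratio will be reported as a point estimate without a standard error. For within-trial comparisons between arms, joint uncertainty in incremental cost and incremental effect will be obtained by cluster-level methods (for example, resampling clusters within arm), with external unit costs varied in sensitivity analysis. It will be shown on the cost-effectiveness plane and as incremental net benefit or an acceptability curve over a stated range of willingness-to-pay values. Any interval for the ratio will use Fieller's method and will be reported whatever its form, including when it is unbounded.*

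The last clause matters: giving the interval only when the effect excludes zero would be a data-dependent rule. The wording should also name the window for the register-based denominator.

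The cost is modest: some extra analysis code, wider intervals, and the need to choose a willingness-to-pay range, which the documents do not give. No new data are needed. Treatment costs drawn from earlier inpatient data and earlier unit costs cannot be resampled by trial cluster, which is why they go into sensitivity analysis.

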## 14. STATISTICS

### 14.1. Sample size justification

Sample sizes were initially calculated assuming a decline from the last National TB Prevalence Survey in 2013-14 given that there has been case-finding activity since then. However, the interim results from a **pre-intervention survey** show greater than anticipated decline (target of 14,511 participants will give precision of +/- 2.5 around an assumed true prevalence of 900 per 100,000 adults, assuming design effect of 1.5 from random household sampling. The increase to 15,500 allows for wastage from e.g. unreadable Xray/contaminated cultures).

Sample size calculations and statistical analyses will use established approaches for cluster-randomised trials.

The **primary trial outcome** has been changed from self-reported testing outcome to TB case notification.

For this, we assume an annual case-notification of adult microbiologically-confirmed TB to be in the range of 70 to 100 per 100,000 adults for the standard of care clusters, based on current data and trends.

An adult population of ~150,000 per arm followed over 12 months will then provide power to detect a 44% to 56% increase in microbiologically confirmed TB if  $k = 0.3$  to  $0.4$ .

Analysis will use standard methods appropriate for cluster-randomised trials, with adjustment for pre-intervention rates of adult microbiologically-confirmed TB.

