| Follow up duration           | 
1-3 months per cluster
 
Pre-intervention survey, 10-11 months of ACF intervention: cluster-initiation will be staggered over 9-months
                                                                                                                                                                                                                                                                                                                                                                   |                                                                                                                                                                                                                                                                                                                                                                                                                                                                                                          |
| Planned recruitment period   | June 2019-Mar 2020: pre-intervention survey and ACF Round 1                                                                                                                                                                                                                                                                                                                                                                                                                                                          |                                                                                                                                                                                                                                                                                                                                                                                                                                                                                                          |

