|                              | Objectives                                                                                                                                                                                                                                                                                                                                                                                                                                                                                                           | Outcome Measures/Endpoints                                                                                                                                                                                                                                                                                                                                                                                                                                                                               |
| 1 Primary Outcome            | 
To determine the impact of TB-ACF on population-level:
 
2.1 Rates of adult registration for microbiologically-confirmed TB
                                                                                                                                                                                                                                                                                                                                                                              | 
To compare between randomisation arms:
 
1.1 The rate of treatment (per 1000 adult residents per year) during the 3 months starting from the first ACF intervention, defined by entry into the District Health Office TB Treatment Register and laboratory records
                                                                                                                                                                                                                           |

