**Figure 1. Original study design.**

[figure not shown]

*Previously undefined abbreviations:* SOC= Standard of Care; k= thousand; mos= months

**Clusters randomised to the ACF intervention arm** will receive 1 round of brief door-to-door enquiry for chronic cough, repeated after 10 months, with staggered cluster initiation over 9 months. Health promotion messaging will be provided at the time of ACF, through leafleting and door-to-door interactions at the time of brief enquiry for chronic cough.

**All clusters (Enhanced Standard of Care):** Irrespective of randomisation, each facility in the study area will be provided with one study staff member (community/environmental health worker) responsible for facilitating identification of attendees with cough for TB investigations and basic infection control; receiving TB or HIV positive clients referred following ACF; and assisting District TB Officers to register patients being investigated for TB, with a special focus on men.

**Outcomes will be evaluated for months 1-3 from ACF initiation** using routine case-notification data for TB case-notification rates.

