### 9.1. Primary and secondary outcomes

The **primary outcome** will compare between arms

1. **The rate of treatment for microbiologically-confirmed TB (per 1000 adult residents per year) during 3 months starting from the first the ACF intervention**, defined by entry into the District Health Office Electronic TB Treatment Register and laboratory records, with cluster resident status of registering TB patients defined by Global Positioning System (GPS) coordinates for place of residence captured by a satellite map application (ePAL) in routine use by Blantyre District TB Officers.

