| 1. Primary Outcome                              | 
To determine the impact of TB-ACF on population-level:
 
2.1 Rates of adult registration for microbiologically-confirmed TB
                                                                                                                                                                                                                                                                                 | 
To compare between randomisation arms:
 
2.1 The rate of treatment (per 1000 adult residents per year) during the 12 months starting from the first ACF intervention, defined by entry into the District Health Office TB Treatment Register and laboratory records
                                                                                                                                                                                                                                                                                               |
| 3 Other pre-planned analyses                    | 
To investigate the impact of TB-ACF on population-level:
 
3.1 Demand for routine TB testing services
 
To determine the impact of provider-initiated HIV self-testing for TB-ACF participants on:
 
3.2 Numbers of newly diagnosed HIV-positive participants, and numbers subsequently linking into HIV care
 
3.3 Numbers of participants diagnosed with TB using sputum microscopy
 | 
To compare between randomisation arms:
 
3.1 The rate (per 1000 adult cluster residents p.a.) of investigation for TB, defined by entry into the “Presumptive TB Register” in selected routine TB Registration Facilities
 
Within clusters randomised to the ACF-arm only, to document rates (per 1000 adult cluster residents p.a.) of:
 
3.2 New diagnosis of HIV made by the ACF team using OraQuick, with follow-up for confirmatory testing and ART initiation
 
3.3 New diagnosis of TB made by the ACF team using microscopy
 |

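### The stated detectable increase of 44% to 56% needs 12 months of follow-up; over the 3-month primary window it is about 84% to 106%

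*Combined protocol and SAP*

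**What the plan says.** The power statement in section 14.1 takes an annual control rate "in the range of 70 to 100 per 100,000 adults for the standard of care clusters" and a between-cluster coefficient of variation k of 0.3 to 0.4. It says that about 150,000 adults per arm "followed over 12 months will then provide power to detect a 44% to 56% increase in microbiologically confirmed TB". It gives no significance level, sidedness or target power.

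The primary outcome is defined over a shorter window:

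- Section 9.1, outcome definition: "during 3 months starting from the first the ACF intervention". The abstract (section 3.5) also gives 3 months.
- Synopsis, primary outcome: "during the 3 months starting from the first ACF intervention".
- Synopsis, follow-up duration: "1-3 months per cluster".
- Section 7: "Outcomes will be evaluated for months 1-3 from ACF initiation".

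The table of objectives in section 9.1 disagrees and gives the same outcome "during the 12 months starting from the first ACF intervention". Section 14.2 defers the detailed analysis plan to a later document, so nothing here settles which window governs.

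**The concern.** Power for a rate comparison depends on the number of events, and a 3-month window holds a quarter of the events of a 12-month one. If the 44% to 56% range was computed on a full year, the trial does not have that power for the outcome it calls primary.

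Two things are at stake. A 3-month result with no clear difference, set against section 14.1, could be taken as evidence against an increase that the analysis would probably have missed. And with two windows in the current text, the primary estimand is not uniquely defined.

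**Working it through.** **Inputs.** 72 clusters allocated 1:1 (section 7), so c = 36 per arm. Section 14.1 supplies 150,000 adults per arm, control rate r0 of 70 to 100 per 100,000 per year, and k of 0.3 to 0.4. Two-sided 5% and 80% power are assumed, giving (1.96 + 0.84)² ≈ 7.85.

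**Formula.** For an unmatched cluster trial comparing rates, with y person-years per cluster:

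c = 1 + 7.85 × [(r0 + r1)/y + k²(r0² + r1²)] / (r1 − r0)²

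This is solved for r1/r0.

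**Reproducing the stated figure (12 months).** y = 150,000/36 = 4,167.

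- r0 = 0.001, k = 0.3, ratio 1.440: Poisson term 0.00244/4,167 = 5.86×10⁻⁷; between-cluster term 0.09 × 10⁻⁶ × (1 + 1.44²) = 2.77×10⁻⁷; squared difference 1.936×10⁻⁷. Then c = 1 + 7.85 × 8.62/1.936 ≈ 36. Detectable increase 44.0%.
- r0 = 0.0007, k = 0.4: the same steps give a ratio of 1.567, an increase of 56.7%. Power at exactly 56% is 79.2%.

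This matches 44% to 56%. With 90% power the range would be 52% to 68%, which does not match. The fit also requires a full year of person-time per resident, so the 12 months cannot mean 3-month windows staggered across a calendar year.

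**The same calculation at 3 months.** y = 37,500/36 = 1,042.

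| Control rate per 100,000 | k | 12 months | 3 months |
|---|---|---|---|
| 100 | 0.3 | 44.0% | 83.6% |
| 100 | 0.4 | 50.1% | 88.6% |
| 70 | 0.3 | 50.9% | 101.4% |
| 70 | 0.4 | 56.7% | 106.3% |

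**Events.** Expected control-arm cases are 150,000 × 0.0007 = 105 to 150,000 × 0.001 = 150 over 12 months, and 26 to 38 over 3 months. That is 0.7 to 1.0 per cluster. With gamma-distributed cluster rates, the chance of no case in a control cluster with mean m is (1 + mk²)^(−1/k²): 37% (m = 1.04, k = 0.3) to 50% (m = 0.73, k = 0.4).

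**Power at 3 months for the planned effects.** z = √[35(r1 − r0)²/V] − 1.96, where V is the bracketed term in the formula.

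- 44% increase, rate 100, k = 0.3: V = 2.62×10⁻⁶, z = √(35 × 1.936×10⁻⁷/2.62×10⁻⁶) − 1.96 = −0.35, power 36%.
- 56% increase, rate 70, k = 0.4: V = 1.99×10⁻⁶, z = √(35 × 1.537×10⁻⁷/1.99×10⁻⁶) − 1.96 = −0.32, power 38%.

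A gamma-Poisson simulation with a cluster-level t-test agreed within 1 to 2 percentage points.

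**Sensitivity at 3 months.** With 160,000 adults per arm (the synopsis figure) the range is 81% to 103%. With k = 0 it is 77% to 95%.

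**The case against.** The strongest reply is that the design may still be adequate. Section 5.1.2 reports that this style of case-finding doubled smear-positive notifications in Harare and Blantyre, and for a true doubling 3-month power is about 76% to 90% across the stated rates and k. That calculation is right, but section 14.1 does not argue for a doubling; it claims power for 44% to 56%. The Harare effect came from 5 rounds over 2.5 years, and the Blantyre programme used 6-monthly enquiry, whereas this trial gives one round.

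A second point is that the 36% to 38% figures carry one rate ratio across both windows. If the effect of a single visit of one to two weeks is concentrated soon after it, the 3-month ratio would exceed the 12-month one. This stands as a caveat. The time-course is itself a research question in section 6.1, so neither pattern can be assumed. It does not affect the detectable-effect range.

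Third, section 14.1 plans adjustment for pre-intervention rates, and randomisation is constrained on notification rates. Both act mainly on between-cluster variance, and removing that variance entirely still leaves 77% to 95%.

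Fourth, section 8.2 keeps the principal investigator and trial statistician blinded until database lock, and section 14.2 requires an analysis plan approved before enrolment is complete. These safeguards reduce the risk that the window is chosen from the results, and a careful reader would judge a null result by its confidence interval. Neither safeguard says which window is primary. The 12-month entry in the section 9.1 table may be left-over text, but it agrees with section 14.1, so it cannot simply be ignored.

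**Conclusion.** The concern holds. The 12-month arithmetic in section 14.1 is sound; the fault is that it belongs to a different window from the primary outcome stated in four places. For a 3-month rate the detectable increase is about 84% to 106%, nearly twice the stated 44% to 56%.

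This rests on two-sided 5% and 80% power, inferred because they reproduce the protocol's own range; on k staying at 0.3 to 0.4 in the shorter window; and on an unadjusted comparison. None of the alternatives tried for population size or between-cluster variation brings the 3-month figure near the stated range. If 12 months is the intended window, the power statement stands and the 3-month definitions are wrong, so a correction is needed on either reading. It must be made before the data are unblinded.

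**What to change.** State one primary window in the abstract (section 3.5), the synopsis (primary outcome and follow-up duration), section 7, section 9.1 (text and table) and section 14.1, and carry it into the analysis plan.

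If 3 months stays primary, replace the power sentence with one such as: with 36 clusters and about 150,000 adults per arm followed for 3 months, a two-sided 5% test has 80% power to detect an increase of 84% to 106%, for control rates of 70 to 100 per 100,000 per year and k of 0.3 to 0.4, before adjustment for baseline rates. Add a sentence on whether one round could plausibly produce an increase of that size. Move the 44% to 56% statement to a pre-specified 12-month secondary rate, noting that an early effect could be diluted over the longer period.

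If 12 months is intended, correct the 3-month entries and add alpha, sidedness and power to section 14.1.

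The cost is protocol wording and, if 3 months is kept, a less favourable detectable effect. The electronic TB register is maintained continuously. With case-finding ending in March 2020 and the study running to August 2021, 12 months per cluster fits the timeline without extra enrolment.
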